### Blinding

Only the research pharmacist responsible for preparing the albumin and placebo will access the computerized random allocation assignment. They will be the only member of the research team to record the allocation.

Blinding of the intervention is difficult since albumin (25%) must be stored in glass containers and is yellow in color while normal saline comes in infusion bags and is transparent. For this pilot trial, the blinding involves administering the placebo (normal saline) in similar glass bottles to those used for the albumin. Both the albumin fluid and placebo will be prepared in advance of administration by the research pharmacist, covered with opaque bags, and primed into opaque intravenous tubing. Furthermore, all members of the clinical and research team will be blinded except the research pharmacist.

### Progression criteria

We will apply the following criteria to make the decision that a definitive trial is worth pursuing, depending on funding and if we can successfully recruit more than 25 patients and enroll 15% of all eligible patients, of whom less than 10% have complications related to the intervention. This pilot trial is to test the study plan and find out whether enough participants will join a larger study and accept the study procedures. The results will be used as a guide for larger studies, and we plan to report our study findings in open-access peer-reviewed journals.

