## Background

The incidence of acute kidney injury (AKI) treated with renal replacement therapy (RRT) in the ICU has more than quadrupled over the last two decades [1–3]. Given the diversity of acute and chronic co-morbidities in patients with RRT-requiring AKI [2], pharmacologic interventions are likely to remain elusive [4]. Nonetheless, efforts to optimize the administration of RRT hold promise for reducing mortality and maximizing the likelihood of renal recovery [5].

The clinical response to hemodynamic instability during slow low-efficiency dialysis (SLED) (or any form of RRT) is often to give intravenous fluid boluses (including albumin (25%)), reduce the ultrafiltration rate, or stop treatment altogether [6, 7]. All of these interventions lead to a more positive net fluid balance in patients with RRT-requiring AKI who usually have minimal urine output. It is unclear if giving fluids in this situation (often with the view to allow further ultrafiltration later on during the same treatment) is beneficial given that (a) simply reducing the ultrafiltration rate alone may lead to adequate time for vascular refilling from the extravascular compartment to improve hemodynamics [6–8] and (b) hemodynamic instability may be unrelated to ultrafiltration/preload reduction [9–11]. This is important given mounting evidence that greater fluid overload in this context is an independent risk factor for increased mortality and longer term dialysis dependence [12–18].

Our recent systematic review found that no studies have previously assessed the efficacy of giving albumin to prevent hypotension or augment fluid removal during SLED [19]. Albumin is frequently used during SLED treatment, and there is lack of data to suggest that albumin is more effective for potentiating fluid removal during SLED as compared with normal saline.

The primary aim of this pilot trial is to determine if, for critically ill patients treated with SLED for AKI, randomization to receive albumin (25%) boluses versus normal saline placebo boluses is feasible, with respect to the recruitment rate, blinding, and adherence to the protocol.

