### Outcome measures

#### Feasibility

Recruitment rate, adherence to intervention, and completeness of follow-up are the principal outcome measures. This study aims to establish that (a) the team can randomize 30 patients into this trial over the study period and (b) trial participants have > 90% adherence to receiving albumin (25%) or normal saline placebo boluses during SLED treatments, as assigned through randomization. For this outcome, each SLED treatment (rather than patient) will be the unit of analysis.

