### Sample size and analytic plan

A total of 30 patients with AKI requiring treatment with SLED (by definition, Kidney Disease Improving Global Outcomes (KDIGO) stage 3 AKI) will be recruited and followed up for this study over the period of 7–14 months at the Ottawa Hospital’s intensive care unit. As this is a pilot study, we do not include a formal sample size calculation. We felt that including 15 patients in each group would inform us about the practical aspects of conducting a larger RCT with respect to study procedures, recruitment, and data collection. Of particular note, this includes determining the average number of SLED sessions received per patient (which will inform the analysis plan for efficacy outcomes for a larger study).

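### The progression criteria contain no adherence criterion, although >90% adherence per SLED treatment is one of the pilot's two numeric feasibility aims

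*Protocol article*

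**What the plan says.** The Background states the primary aim as whether randomization to albumin or saline boluses "is feasible, with respect to the recruitment rate, blinding, and adherence to the protocol".

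The Feasibility section under Outcome measures says: "Recruitment rate, adherence to intervention, and completeness of follow-up are the principal outcome measures". It then gives two numeric aims. The first is that "the team can randomize 30 patients into this trial over the study period". The second is that "trial participants have > 90% adherence to receiving albumin (25%) or normal saline placebo boluses during SLED treatments", with the SLED treatment, not the patient, as the unit of analysis. Completeness of follow-up gets no number there or elsewhere in the article.

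The Progression criteria section opens: "We will apply the following criteria to make the decision that a definitive trial is worth pursuing". Apart from funding, the conditions are that the team can "successfully recruit more than 25 patients and enroll 15% of all eligible patients, of whom less than 10% have complications related to the intervention". Neither adherence, follow-up nor blinding appears.

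The Discussion gives adherence and follow-up a use after the pilot: refining the final protocol and adjusting sample size estimates.

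**The concern.** The go/no-go decision is the main product of a feasibility pilot, so the rule for it should reflect the questions that the pilot was set up to answer. Here one of the two outcomes with a stated target does not enter the rule.

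This is not a remote risk. The Intervention section itself notes that mid-treatment boluses may be missed when the patient is hemodynamically stable. The Progression criteria section goes on to say that the pilot tests whether participants accept the study procedures, but none of its criteria measures whether those procedures were delivered.

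Low adherence would shrink the contrast between arms in a definitive trial, so it bears directly on whether such a trial can answer its question. If the role of adherence is left open until the data are in, deciding then whether it counts would be post hoc.

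**Working it through.** **1. The plan's own number.** The Sample size and analytic plan section gives "A total of 30 patients with AKI requiring treatment with SLED" and says that "including 15 patients in each group would inform us about the practical aspects of conducting a larger RCT". 2 × 15 = 30, which reproduces the total. The article disclaims a formal sample size calculation, so there is no power figure to check.

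**2. Aims against progression criteria.**

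| Item | Aim (Background; Outcome measures) | Progression criteria |
|---|---|---|
| Patients recruited | 30 | more than 25 |
| Share of eligible patients enrolled | no figure | 15% |
| Adherence per SLED treatment | more than 90% | none |
| Completeness of follow-up | principal outcome, no figure | none |
| Blinding | in the primary aim, no figure | none |
| Complications | no figure | less than 10% of those enrolled |

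Adherence is the only row with a numeric aim and no counterpart in the rule.

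**3. Can a pilot fail the adherence aim and pass the rule?** Take 50% adherence as an example.
- Recruitment: 30 patients meet the aim, and any number from 26 also passes the rule.
- Share of eligible: the Limitations section assumes a consent rate of 20%. If that is read as the enrolled share, 30 / 0.20 = 150 eligible patients. Then 30/150 = 20.0% and 26/150 = 17.3%, both above 15%. With 26 enrolled, the criterion holds for up to 173 eligible patients (26 / 0.15 = 173.3).
- Complications: two or fewer pass (step 5).
- Adherence: not consulted.

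So every listed criterion can be met at 50% adherence, or at any other level.

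**4. What the >90% figure would require.** The article does not give the number of sessions per patient, so 2, 3 and 5 are assumed, with 26 patients.

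| Sessions per patient (assumed) | Total sessions | Fewest adherent sessions above 90% | Adherent sessions at 50% |
|---|---|---|---|
| 2 | 52 | 47 | 26 |
| 3 | 78 | 71 | 39 |
| 5 | 130 | 118 | 65 |

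**5. The complication limit.** The largest count k with k/N < 0.10 is 2 for every N from 26 to 30.
- N = 26: 2/26 = 7.7% passes; 3/26 = 11.5% fails.
- N = 30: 2/30 = 6.7% passes; 3/30 = 10.0% is not below 10% and fails.

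If both events fall in the albumin arm and the arms are equal, the rate in that arm is 2/13 = 15.4% or 2/15 = 13.3%.

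**6. Would a limit within each arm be better?** Exact binomial probabilities with 15 per arm, where less than 10% means at most 1 event per arm or at most 2 pooled. All true rates are assumptions.
- True 5% in both arms: the pooled rule passes with P(X ≤ 2 | 30, 0.05) = 0.81. Requiring both arms to pass gives P(X ≤ 1 | 15, 0.05)² = 0.829² = 0.69.
- True 20% on albumin and 0% on saline: pooled 0.40, albumin-arm rule 0.17.
- True 15% on albumin and 0% on saline: pooled 0.60, albumin-arm rule 0.32.

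The within-arm rule catches more albumin-only harm, but it also stops more often when the true rate is acceptable.

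**The case against.** The best defence is that adherence is not ignored. It is monitored throughout (Intervention), it feeds protocol refinement and sample size (Discussion), and the article describes the next step as a multi-center pilot, where delivery problems could be corrected. The progression section also calls the results a guide, so the criteria need not trigger progression automatically. This stands as far as it goes: 50% adherence passes only if the list is read as sufficient. But the section presents the list as the criteria for the decision, and nothing explains why a stated >90% aim is left out of it.

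A reader might infer more than the documents support, in four ways.

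- **That more than 25 contradicts 30.** A minimum for progression set below the target is an ordinary choice, and the Discussion says that a lower recruitment rate would lead to more sites or a longer recruitment period. Only the label is missing.
- **That follow-up needs a threshold too.** The article sets no numeric follow-up target, so any figure would be the reviewer's own. The same holds for blinding.
- **That two of the three principal outcomes have no influence at all.** The Discussion gives both adherence and follow-up a role; what they lack is a place among the criteria.
- **That the <10% limit must apply within each arm.** The wording attaches the limit to all enrolled patients, and with about 15 per arm a single patient decides the result. The contrast of 0.40 with 0.17 rests on assumed rates of 20% and 0%, which favour the within-arm rule. At a true 5% in both arms, that rule lowers the chance of passing from about 0.81 to 0.69. It is a trade-off, not a correction.

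**Conclusion.** The point holds for adherence. The article puts it in the primary aim, names it a principal outcome and gives it a target above 90% per SLED treatment, then omits it from the criteria for a definitive trial. A pilot at 50% adherence would miss that target and could satisfy every listed condition. This follows from the text and needs no assumption about event rates or sessions per patient, only that the listed criteria are applied as written.

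The recruitment floor and the pooled complication limit are matters of clarity. The range of 13.3% to 15.4% on albumin assumes equal arms and both permitted events on albumin. It shows what the pooled limit allows, not what is likely.

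No participant's treatment and no estimate is affected. What is at stake is the soundness of the go/no-go decision, so the text should be settled before results are known.

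**What to change.** In the Progression criteria section, add adherence above 90%, with the SLED treatment as the unit, exactly as in the Feasibility section under Outcome measures. State that a shortfall means progression only with protocol changes, not an unconditional go.

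Two minor additions:
- Say that more than 25 patients is the minimum for progression against a target of 30.
- Report complications by arm beside the pooled <10% limit. This can be tabulated once the pilot has ended, so the blinding arrangements need not change.

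The cost is a few sentences. Adherence is already to be monitored and adverse events tracked, so no new data are needed. The downside is a slightly harder bar for an unconditional go.

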### Study measurement and patient safety

A trial management group involving the principal investigators ([name]), four co-investigators ([name]), and two study coordinators ([name]) will review, implement, and supervise all aspects of this pilot trial. All investigational product supplies in the study will be stored in a secure, safe place, under the responsibility of the investigators. The statistical analysis will be conducted by the investigators ([name]). The results will be disseminated via conferences and publication in an open-access publication and the trial registry; decision for publication lies with the investigators. The reporting of the results will follow the CONSORT statement- extension for Pilot and Feasibility Studies [20]. We will also continue to monitor and track any adverse events throughout this trial and report as necessary.

## Discussion

The results of the pilot trial will provide crucial data to the planning of a multi-center pilot randomized trial to determine if albumin (25%) boluses are as effective as normal saline boluses for improving hemodynamic stability and promoting fluid removal using SLED. A lower recruitment rate will help us to plan to add more sites or a longer recruitment period for the multi-center pilot trial. Protocol adherence and follow-up measurements will provide additional feasibility information to plan refinement of the final protocol as well as adjust sample size estimates for a larger trial. As well, the pattern of SLED use for enrolled patients (i.e., number of sessions per patient and determination of which sessions typically involve ultrafiltration/fluid removal) will help determine the optimal design of a larger trial with respect to whether randomization should occur at the patient or SLED treatment session level as well as the optimal number of treatments to consider for analysis.

If the results of a large multi-center trial showed that albumin boluses are effective in this setting then their wider-spread use might be warranted given mounting evidence that greater fluid overload in critically ill patients with AKI is associated with increased morbidity and mortality. If shown to be ineffective, the cost savings from decreased albumin use would be substantial.

### Limitations

The study design has certain limitations. Since this is a pilot trial, it will be underpowered to demonstrate efficacy; however, the potential efficacy data will allow planning for a larger trial. In addition, given the challenges of obtaining informed consent from critically ill patients, we conservatively assume a consent rate of only 20%. Even so, there should be a sufficient number of patients receiving SLED for AKI within less than 24 months.

### Trial status

This trial has received grant funding from The Department of Medicine, The Ottawa Hospital and the University of Ottawa in 2017, as well as obtained approval from the Ottawa Health Sciences Research Ethics Board on October 5, 2018. Patient recruitment will begin in April 2019.

## Data Availability

Data from the trial will be made available following institutional policies.

## Abbreviations

AKI: Acute kidney injury
CRRT: Continuous renal replacement therapy
DMS: Data Management Services
ICU: Intensive care unit
IV: Intravenous
KDIGO: Kidney Disease Improving Global Outcomes
SAFER: Saline versus albumin for extracorporeal removal
SLED: Slow low-efficiency dialysis
TOH: The Ottawa Hospital
